## Discussion

To our knowledge, this will be the first trial with an adaptive intervention to test the effectiveness of using a smartphone app to increase the level of physical activity of adults and older adults. As stated above, the SMART design has been recommended over the classical randomized controlled trial for technology-based interventions [12, 13].

One of the major challenges of the present study will be to engage Brazilians to track their daily steps using technology. Despite the large number of smartphones in use in Brazil, whether the proposed application will be effective in this population needs more clarification. Another challenge will be the lack of security to carry out outdoors physical activities in Brazil, regardless of the neighborhood. In our recent experience, many participants from our pre-test reported not using a smartphone when practicing physical activity outdoors. We believe that creating favorable conditions for behavior change and the adoption of a healthy lifestyle will favor adherence and engagement of those involved in the study. Using the technology available on a smartphone to encourage the adoption of new ways of thinking and acting can be a new way of promoting the quality of life and well-being of the Brazilian population.

Finally, the sample size required for SMART studies is usually large and difficult to calculate. We are aware of the difficulty of involving enough people in a tight timeline. However, we are confident that we are prepared to run the protocol with sufficient statistical power, at least for some key health variables.

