## Background

Popular technologies such as smartphones and their applications (apps) have been used as tools to engage people who do not meet the recommended levels of physical activity. There is scientific evidence with moderate effect (weighted effect size = 0.54) suggesting that app-based interventions targeted to increase the level of physical activity might be effective [1], although multi-component interventions appear to be more effective than app-based interventions alone [2]. Apps intended to improve cardiovascular health should include features such as privacy policy and reliable sources of information and should be mainly designed using behavior change theory [3]. It is believed that the development of apps based on behavioral change techniques may contribute to the emergence of cognitive patterns favorable to the practice of physical activity.

The main effective components of apps are most likely personalization and gamification [4]. Interestingly, the adherence rate to an app-based intervention was not significantly different in comparison to conventional intervention [5]. However, despite its increasing use, smartphone apps for physical activity lack a scientific basis. Among many health and fitness apps, only a few are based on behavior change techniques [2, 6–8].

The use of games for promoting healthy lifestyle behaviors (such as physical activity) has been shown to be effective [9], introducing gaming elements as novel opportunities for behavior change techniques, increasing enjoyment and, thus, intrinsic motivation. The use of game elements outside of the game context is called gamification and has been increasingly used for promoting healthy lifestyle behaviors. Among gaming elements, goal-setting with feedback and rewards are the most frequently used. Social connection, progress bars, and challenges/quests have also been investigated in a smaller number of studies [10]. Studies have also shown that there is a limited theoretical foundation for gamification, and most studies have used goal-setting as a motivation strategy to engage people in playing the game [10].

Among the main limitations of the available apps, with or without game elements, is the long-term adherence to app-based interventions [10, 11]. Despite the motivating results, it remains unclear whether or not app-based interventions can increase the level of physical activity and cardiovascular health.

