### Aims and design

The primary aim of our study is to investigate the effect of a smartphone app combined with game elements on the level of physical activity of adults and older adults, measured by the average number of daily steps. The secondary aims are (1) to verify the effects of the intervention on cardiometabolic and cardiovascular health, lung function, and cardiorespiratory fitness; and (2) to verify the relationship between age group and the response rate.

We will conduct a Sequential Multiple Assignment Randomized Trial (SMART). This study was approved by the Ethics Committee of the Federal University of Sao Paulo (# 0499/2018) and is registered in the Brazilian Clinical Trials Registry (RBR-8xtc9c).

The SMART design has been recommended over the classical randomized controlled trial for technology-based interventions [12, 13] as it allows adaptations over time based on the participants’ response to the intervention. Despite the large potential and shown feasibility [14], the SMART design has, thus far, hardly been conducted in smartphone and gamified interventions.

The adaptive intervention protocol will last 6 months. Initially, participants will be randomized into one of three groups (group 1: app + tailored messages; group 2: app + tailored messages + gamification I; control group: physical activity counseling) (Fig. 1). Over 12 weeks, we will record the average number of steps per day for each participant from groups 1 and 2. At 6 weeks from initiation, participants will be classified into responders and non-responders according to the targeted average number of daily steps; all those considered as non-responders will be re-randomized, with the chance to participate in a third group – group 3: app + tailored messages + gamification II (Fig. 1). At the end of the 12 weeks, participants will continue using the app but will no longer receive any direct intervention from investigators. All participants, including those in the control group, will be reassessed at 3 and 6 months from baseline. The protocol timeline is shown in Fig. 2.

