### Sample size

The main objective of a SMART study relies on the feasibility of carrying out a future large-scale trial, rather than investigating the effects of the proposed set of treatments. To reach this goal, we must ensure that the number of subjects will be sufficient and balanced among all of the subgroups. According to Almirall et al. [16], a fixed probability *k* of about 80–90% should be considered so that at least *m* participants would end in non-responders’ subgroups B, C, E and F (Fig. 1). Considering a range of non-response rates in SMART studies of 35–65%, we calculated an *m* of 3 participants per subgroup as sufficient to ensure familiarity with the protocol, treatment delivery, and identification of potential problems. For a non-response rate of q = 50% at the end of the 6th week, our pilot SMART study will require 42 participants (14 per arm) [16].

After conducting this SMART pilot, we will consider the variation on the average number of steps per day to calculate the sample size of the trial, including an up to 40% loss to follow-up and a less optimistic non-response rate of 65%. To increase the feasibility of a future large-scale trial, we will calculate the sample size considering groups A + B (maintain – switch to group 2), groups A + C (maintain – switch to group 3), groups D + E (maintain – switch to group 1), groups D + F (maintain – switch to group 3), and the control group.

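### The plan states an effect aim, tests of effect and sufficient power, but its only sample size (42, 14 per arm) is set for feasibility and no calculation supports the power statement

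*Protocol article*

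**What the plan says.** Four places in the protocol article bear on this.

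- **Aims and design:** this section begins with an effect aim, "The primary aim of our study is to investigate the effect of a smartphone app combined with game elements", and the measure is average daily steps. The study is not split into a pilot and a trial here.
- **Sample size:** here the stated objective "relies on the feasibility of carrying out a future large-scale trial, rather than investigating the effects of the proposed set of treatments". The 42 participants (14 in each of three arms) follow from a rule that at least m = 3 people reach each of the non-responder subgroups B, C, E and F with probability k of about 80–90%, "For a non-response rate of q = 50% at the end of the 6th week". The size of the trial proper is to be worked out after the pilot, and no number is given.
- **Data analysis:** ANOVA compares A+B+C and D+E+F with control on activity, cardiovascular and metabolic health, lung function and fitness. For daily steps it also compares the final subgroups A to F, and the combinations A+F, B+D and C+E, with control. No stage is named.
- **Discussion:** after remarking that SMART sample sizes are large and hard to calculate, the authors write "we are confident that we are prepared to run the protocol with sufficient statistical power, at least for some key health variables".

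The only effect size in the article is in the Background ("weighted effect size = 0.54"), given as existing evidence on app-based interventions and physical activity.

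**The concern.** The effect aim and the ANOVA comparisons are written as if the study under way could answer them. The Sample size section says the opposite about the only cohort whose size is known. The Discussion then adds a power statement with no N, alpha, effect size, SD or named outcome behind it. A reader cannot tell which statement governs the 42 participants.

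Two misreadings could follow. A non-significant ANOVA in 42 people could be taken as evidence that the app does not work, when the study had little chance of showing a moderate effect. A significant one needs a large observed difference at this size, so if the true effect is moderate, the significant estimates would tend to overstate it. The single-subgroup comparisons, with three or four people in a cell, are the most exposed.

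**Working it through.** **1. Reproduce the plan's own figure.** Inputs from the Sample size section: n = 14 per arm, q = 0.5, m = 3. Re-randomised non-responders split between two subgroups, so an arm needs at least 2m = 6 non-responders if the split is even.

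P(X ≥ 6), X ~ Bin(14, 0.5) = 1 − 3473/16384 = 0.788.

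This is close to the lower end of the 80–90% range, so 14 per arm is reproduced when k is read per arm. The rule uses only m, k and q. No alpha, power, effect size or SD enters it, so it says nothing about power for an effect. The expected size of a non-responder subgroup is 14 × 0.5 / 2 = 3.5.

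**2. What 14 per arm can detect.** Assumptions, because the article states no alpha or sidedness: two-sided 5%, unadjusted comparison of two means, no loss, effects in SD units.

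Power = P(|T| > t₀.₉₇₅,df), where T is noncentral t with df = n₁ + n₂ − 2 and noncentrality δ = d·√(n₁n₂/(n₁+n₂)).

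For 14 v 14: df = 26, critical value 2.056, √(196/28) = 2.646. Power reaches 80% at d ≈ 1.10 (δ = 1.10 × 2.646 = 2.91). This result does not depend on the Background's effect size.

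**3. Illustration at d = 0.54.**

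| Comparison | df | δ | Power |
|---|---|---|---|
| One app arm v control, 14 v 14 | 26 | 0.54 × 2.646 = 1.429 | 28% |
| Both app arms v control, 28 v 14 | 40 | 0.54 × 3.055 = 1.650 | 36% |
| Subgroup of 4 v 14 | 16 | 0.54 × 1.764 = 0.952 | 15% |
| Subgroup of 3 v 14 | 15 | 0.54 × 1.572 = 0.849 | 13% |

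For scale, 80% power at d = 0.54 needs 55 per arm with data.

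**4. Sensitivity to the assumptions.** Data analysis speaks of pre- and post-intervention, so baseline may be used. Adjusting for a baseline that correlates r with the outcome raises the effective effect to d/√(1 − r²). No correlation is given, so r is assumed (14 v 14, df kept at 26; spending one df on the covariate changes power by less than one percentage point):

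- r = 0.5: 0.54/0.866 = 0.624, power 36%
- r = 0.7: 0.54/0.714 = 0.756, power 49%
- r = 0.8: 0.54/0.600 = 0.900, power 63%

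In the other direction, halving alpha for two comparisons with control (2.5% each, unadjusted) gives 19%. None of these variants reaches 80%.

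**The case against.** The strongest reply is that the Discussion sentence is about the later trial. The Abstract and Sample size section describe a pilot followed by a trial sized from its results, the sentence comes straight after a remark on large SMART samples, and recruitment runs from October 2018 to November 2020, long for 42 people. This stands as a possible reading. It does not rescue the sentence, because the later trial has no stated size from which power could follow. The text also never says that this is the meaning.

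Second, the sentence covers only some key health variables, while 0.54 concerns physical activity and is never adopted as a design effect. This also stands. A reader might infer that 28% power refutes the sentence. The documents do not support that, since they name no health variable and give no effect size for one. What can be said is that any such variable would need a difference of about 1.10 SD at 14 per arm in an unadjusted comparison.

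Third, 28% depends on unstated choices of alpha, sidedness and adjustment. That is correct, and the figure should not be printed in the protocol as the study's power.

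Fourth, a reader might apply the 40% loss allowance to the 42 and report still lower power. The Sample size section gives that allowance for the later trial only, so it is not used here.

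Fifth, the Sample size section already calls the 42 a pilot with a feasibility objective. True, but Aims and design and Data analysis do not carry that through.

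**Conclusion.** The point holds as an unresolved boundary between pilot and trial, together with a power statement that no figure in the article supports. The effect aim and the feasibility objective cannot both be the main purpose of the same 42 participants.

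The conclusion on size is conditional. If the Discussion sentence means the 42, the design does not deliver it: about 1.10 SD is detectable with 80% power at 14 v 14, under an assumed two-sided 5% unadjusted comparison with no loss. The power figures at 0.54 (28% for 14 v 14, 36% for 28 v 14, 13–15% for a subgroup of 3–4 v 14, and about 36–63% with baseline adjustment at assumed correlations of 0.5–0.8) are illustrations.

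If the sentence means the later trial, it is unsupported and not shown to be false. The documents do not justify the stronger conclusion that the whole programme is underpowered.

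**What to change.** - **Aims and design, Data analysis and Discussion:** state which aims and analyses belong to the 42-participant pilot and which to the later trial.
- **Pilot:** make feasibility the primary objective, in line with the Sample size section. Report group and subgroup differences as exploratory estimates with 95% confidence intervals, and draw no conclusion on effectiveness.
- **Later trial:** keep the effect on daily steps as its primary aim, so that the aim is moved to the right stage and not lost.
- **Power sentence:** delete it, or tie it to a stated stage, N, alpha, outcome and effect size.

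This changes wording only and adds no participants. The cost is a less favourable power statement.

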### Trial status

The study is currently recruiting participants. Recruitment began on 15 October 2018, and is intended to be completed on 15 November 2020.

**Protocol version and date:** Version number 4, 23 October 2019.

## Data Availability

The data that support the findings of this study will be available from the authors upon reasonable request and with permission of [name].

## Abbreviations

app: application
FVC: forced vital capacity
FEV1: forced expiratory volume in the first second
SMART: Sequential Multiple Assignment Randomized Trial
SPIRIT: Standard Protocol Items: Recommendations for Interventional Trials
